## Abstract

**Background:**

The misuse and overuse of antibiotics contribute to the acceleration of antimicrobial resistance (AMR), but public knowledge on appropriate antibiotic use and AMR remained low despite ongoing health promotion efforts. App gamification has gained traction in recent years for health promotion and to affect change in health behaviors. Hence, we developed an evidence-based serious game app “SteWARdS Antibiotic Defence” to educate the public on appropriate antibiotic use and AMR and address knowledge gaps.

**Objective:**

We aim to evaluate the effectiveness of the “SteWARdS Antibiotic Defence” app in improving the knowledge of, attitude toward, and perception (KAP) of appropriate antibiotic use and AMR among the public. The primary objective is to assess the changes in KAP of antibiotic use and AMR in our participants, while the secondary objectives are to assess the extent of user engagement with the app and the level of user satisfaction in using the app.

**Methods:**

Our study is a parallel 2-armed randomized controlled trial with a 1:1 allocation. We plan to recruit 400 participants (patients or their caregivers) aged 18-65 years from government-funded primary care clinics in Singapore. Participants are randomized in blocks of 4 and into the intervention or control group. Participants in the intervention group are required to download the “SteWARdS Antibiotic Defence” app on their smartphones and complete a game quest within 2 weeks. Users will learn about appropriate antibiotic use and effective methods to recover from uncomplicated upper respiratory tract infections by interacting with the nonplayer characters and playing 3 minigames in the app. The control group will not receive any intervention.

**Results:**

The primary study outcome is the change in participants’ KAP toward antibiotic use and AMR 6-10 weeks post intervention or 6-10 weeks from baseline for the control group (web-based survey). We will also assess the knowledge level of participants immediately after the participant completes the game quest (in the app). The secondary study outcomes are the user engagement level (tracked by the app) and satisfaction level of playing the game (via the immediate postgame survey). The satisfaction survey will also collect participants’ feedback on the game app.

**Conclusions:**

Our proposed study provides a unique opportunity to assess the effectiveness of a serious game app in public health education. We anticipate possible ceiling effects and selection bias in our study and have planned to perform subgroup analyses to adjust for confounding factors. The app intervention will benefit a larger population if it is proven to be effective and acceptable to users.

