#### Inclusion and Exclusion Criteria

Participants must be older than 18 years, be a visitor of National Healthcare Group (NHG) polyclinic, have access to an Android smartphone, and be able to comprehend the English language to be eligible for the study. Those who are unable to install Android app, not proficient with smartphone apps, and have visual or cognitive impairment will be excluded from the study.

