### Statistical Analysis

We will analyze the changes in the KAP scores with multivariable linear regression models and app satisfaction levels among intervention group participants with descriptive analyses. We will also conduct a post hoc power analysis to ensure that the sample size used in our study is adequately powered to detect a significant change.

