### Potential Limitations

Health promotion efforts to improve the public’s knowledge of antibiotics use are ongoing in Singapore via traditional mass media such as posters, advertisements, and billboards. These advertisements may contaminate and dilute the effects of our intervention but should not have a measurable impact on our study as the study period falls outside the national “antibiotic awareness week” campaign. Participants with good baseline knowledge may not see knowledge improvement due to the ceiling effect. We anticipate this problem to be minor, as a recent national study found that knowledge of good antibiotic use and AMR is poor among the population.

We will also ensure that only 1 adult from each household can participate in the study to minimize the possibility of contamination due to randomization (ie, 1 member is randomized into the control group and another into the intervention group). However, we would not be able to ensure that the recruited participant is the person completing the quest in the app, as family members (ie, children) may help to complete the game quest.

Older adults who are not technologically astute may also be excluded from our study or face difficulty in completing the game quest even if they meet the inclusion criteria. We will report problems with recruitment and follow-up and conduct subgroup analyses to assess outcomes between older and younger participants.

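### Subgroup analyses cannot adjust for confounding, the one described compares outcomes rather than the app's effect by age, and the eligible age range is contradictory

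*Protocol article*

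**What the plan says.** Abstract, Conclusions: having anticipated a ceiling effect and selection bias, the team say in the same sentence that they "have planned to perform subgroup analyses to adjust for confounding factors".

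Discussion, Potential Limitations, is the only place in the body that mentions subgroups. It notes that "Older adults who are not technologically astute may also be excluded from our study", and the team will then "conduct subgroup analyses to assess outcomes between older and younger participants". The same section acknowledges that "Participants with good baseline knowledge may not see knowledge improvement due to the ceiling effect", expects this to be minor, and attaches no analysis to it.

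Methods, Statistical Analysis: "We will analyze the changes in the KAP scores with multivariable linear regression models". It does not mention subgroups, and the covariates are not listed.

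On age, the Abstract (Methods) plans to recruit people "aged 18-65 years from government-funded primary care clinics in Singapore". The Inclusion and Exclusion Criteria say "Participants must be older than 18 years, be a visitor of National Healthcare Group (NHG) polyclinic", with no upper limit.

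**The concern.** Subgroup analysis is given a task it cannot perform. Splitting the enrolled sample produces smaller comparisons within strata. It does not adjust the arm comparison for anything, bring back people who were never enrolled, or remove a ceiling from the instrument. A reader of the Abstract would think these threats have an analytic remedy, and the body does not contain one.

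The one subgroup analysis described is also aimed at a different question. Older and younger people may differ in KAP change whatever their arm. The useful question is whether the difference between app and control varies with age, and that is a question about an interaction.

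The age statements raise a separate problem: they decide who may be enrolled, and they disagree.

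**Working it through.** **Purpose against method**

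- *Confounding.* Allocation is randomised 1:1, so confounding of the arm comparison by baseline factors is dealt with by design. Chance imbalance is handled by covariates in the planned regression, not by splitting the sample.
- *Selection.* The people of concern are older adults who never enter the trial. No split of those who do enter recovers them.
- *Ceiling.* A ceiling on the 11-item knowledge score is a property of the instrument and of baseline knowledge. An age split does not remove it. An arm-by-baseline-score term could describe it, but none is mentioned.

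**Age statements side by side**

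| Person | Abstract, Methods | Inclusion criteria, read literally |
|---|---|---|
| Aged 18 | eligible | not eligible |
| Aged over 65 | not eligible | eligible |

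**How much an age analysis can show**

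Inputs from Sample Size: standardised effect 0.334, two-sided alpha 0.05, power 80%, 142 per group, 30% attrition, 200 per group.

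1. The plan's own figure: n = 2(1.960 + 0.842)²/0.334² gives 141 by the normal approximation; the t-test gives 141.7, so 142 is reproduced. Inflation: 142/0.70 = 203 against the stated 200, which is close enough.
2. Evaluable per arm: 200 × 0.70 = 140.
3. The documents give neither an age cut-off nor the older share. I assume 50% down to 10% older, equal arms within each age group, and SD 1 in both.
4. Interaction standard error: SE = √(2/n_old + 2/n_young), with n per arm. The interaction detectable with 80% power is 2.80 × SE. Power values use the normal approximation.

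| Older share | Older / younger per arm | Power in older group for 0.334 SD | Interaction SE | Detectable interaction | Power for an interaction of 0.334 SD |
|---|---|---|---|---|---|
| 50% | 70 / 70 | 51% | 0.239 | 0.67 SD | 29% |
| 30% | 42 / 98 | 33% | 0.261 | 0.73 SD | 25% |
| 20% | 28 / 112 | 24% | 0.299 | 0.84 SD | 20% |
| 10% | 14 / 126 | 14% | 0.398 | 1.12 SD | 13% |

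With 70 per arm the t-test gives 50% rather than 51%. Even at an equal split, the detectable interaction is twice the design effect (0.67/0.334 = 2.0). These figures are for two age groups. A continuous age term would differ somewhat, depending on an age distribution that is not given.

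**The case against.** The strongest reply is that the faulty phrase sits in an abstract. The body plans multivariable regression, where adjustment belongs, and never says that subgroups adjust for anything. Potential Limitations already presents the exclusion of less technologically able older adults as a limitation and promises to report recruitment problems. Whether age is examined by strata, by interaction or only descriptively is a detail a condensed article may leave to an analysis plan. Much of this stands and keeps the point modest. It does not make the Abstract's claim correct, and it does not touch the age conflict, because condensing a protocol does not explain two incompatible statements in one article.

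Four stronger readings are tempting, and the document does not support them:

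- *That subgroup analyses are meant to adjust for the ceiling effect and selection bias.* The sentence invites this, but the literal object of the adjustment is confounding factors. The claim is wrong on either reading.
- *That separate significance tests by age will mislead.* With an identical true effect and an even split, the chance that exactly one half is significant would be about 2 × 0.506 × 0.494 = 50%. No section plans such tests, so this is a risk to rule out and not a fault in the plan.
- *That the age comparison depends on the contradicted age range.* No cut-off is stated, and a split can be made under either range. The absence of a cut-off is not held against the article.
- *That baseline score is left out of the model.* The covariates are not listed, so its omission cannot be assumed.

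**Conclusion.** The point holds in two separate parts. First, the Abstract credits subgroup analysis with adjustment it cannot provide, and the only one described, as worded, compares outcomes by age and not the app's effect by age. Second, the eligible age range is contradictory at both ends.

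The size is moderate. The sample size reproduces, and the randomised primary comparison stands. Any age analysis will be weak: under the assumed shares, power is 13% to 29% even for an interaction as large as the whole design effect. These figures rest on 30% attrition and on older shares that are assumed, not documented. The confounding and eligibility points need no figures.

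**What to change.** 1. Delete the adjustment claim from the Abstract's Conclusions, and treat selection as a limit on generalisability there, in line with Potential Limitations.
2. State that the baseline KAP score is a covariate in the regression under Statistical Analysis, for precision and chance imbalance. This does not remove a ceiling and should not be described as doing so.
3. Replace the comparison of outcomes by age with an arm-by-age interaction in that model, and add an arm-by-baseline-score interaction to describe any ceiling. Label both exploratory, report estimates with confidence intervals, and draw no conclusion from separate subgroup p-values.
4. Reconcile the Abstract's Methods and the Inclusion and Exclusion Criteria to one age range, explicit at both ends.

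The cost is wording, one covariate from the baseline survey already collected, and the terms for two interactions. No new data or participants are needed. The downside is that the interaction tests have low power, so a null result must not be read as evidence that the app works equally well at all ages.

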**Trial Registration:**

ClinicalTrials.gov NCT05445414; https://clinicaltrials.gov/ct2/show/NCT05445414

**International Registered Report Identifier (IRRID):**

DERR1-10.2196/45833

## Introduction

### Background

Antimicrobial resistance (AMR) has been a long-standing public health threat since the 1940s [1]. The widespread use of antibiotics has accelerated the growth of antibiotic-resistant bacteria, which can cause infections that are fatal and resistant to treatment [1]. In 2019, 4.95 million and 1.29 million global deaths were associated with and attributable to bacterial AMR [2]. It is estimated that 10 million global deaths will be attributable to AMR annually if no action is taken to tackle the problem [3].

AMR infections are often costly to health systems due to the excess length of hospital stays, more outpatient visits, and increased use of intensive care and isolation units [4]. For example, a methicillin-resistant *Staphylococcus aureus* infection could result in an additional US $31,338 (~SGD $42,620) hospitalization cost per patient [5]. AMR infections can also incur societal costs in terms of loss in work productivity and the risk of further infections [6,7].

The misuse and overuse of antibiotics are major drivers of AMR [8]. One pertinent factor contributing to the misuse of antibiotics is the public’s knowledge deficit of the indication for and proper use of antibiotics [9]. This knowledge deficit often leads to unnecessary patient demand for antibiotics and subsequent misuse of antibiotics [10,11]. Knowledge deficit in antibiotic use and AMR was consistently present among populations worldwide [12]. A nationally representative survey conducted in 2021 on adult Singaporeans demonstrated the association between poor knowledge of antibiotics and inappropriate use [9]. The study also showed that younger adults with poor knowledge had a higher likelihood of misusing antibiotics when compared with older adults, highlighting the need to address knowledge deficits on antibiotic use among the younger population in Singapore to mitigate the problem of AMR in the community [9].

### Rationale for the Study

Traditional mass public educational efforts using brochures, posters, and advertisements are extensive in outreach but questionable in improving the general public’s knowledge on appropriate antibiotic use and AMR [13,14]. In recent years, gamification—the use of game-playing elements to encourage the use of services—has gained attention as a novel strategy to affect change in health behaviors [15,16]. Increased user engagement can potentially lead to higher knowledge gains and retention for sustained behavioral change. Gamification was found to improve the knowledge of AMR. For example, a study found that the E-bug student website significantly increased the knowledge of appropriate antibiotic use among schoolchildren in the United Kingdom [17]. Another study using an web-based board game also found significant improvement in medical students’ knowledge of AMR immediately and 1 month post intervention [16]. These proof-of-concept studies support the effectiveness of gamification in increasing knowledge on appropriate antibiotic use among young people, which should be strengthened with randomized controlled trials along with other segments of the population and age groups.

### Hypothesis and Objectives

The public has low awareness of the gravity of AMR as many people perceive AMR as a nonimminent life-threatening problem for themselves [18]. We expect serious games to increase user engagement in learning, which leads to short- and long-term improvements in knowledge of, attitude toward, and perception (KAP) of the appropriate use of antibiotics. Leveraging digital technology to increase the awareness of AMR and the knowledge of appropriate antibiotic use is timely as Singapore develops into a digitalized nation. Hence, we have developed an evidence-based serious game app, “SteWARdS Antibiotic Defence,” to educate the public on appropriate antibiotic use and AMR. Users will learn about antibiotic use and AMR through the minigames and the bite-sized information released from the app.

We aim to evaluate the effectiveness of the “SteWARdS Antibiotic Defence” app in improving the KAP of appropriate antibiotic use and AMR among the public in Singapore. The primary objective is to compare the changes in KAP of antibiotic use and AMR among the app users with the control group. The secondary objectives are to assess (1) the extent of user engagement with the app by evaluating the users’ average screen time per day and (2) the level of user satisfaction in using the app for learning through a user satisfaction survey.

## Methods

### Study Design

Our study is a parallel 2-armed randomized controlled trial (RCT) assessing the effectiveness of a serious game app in increasing the knowledge and changing the attitudes and perceptions about appropriate antibiotic use and AMR among the public. Participants randomized to the intervention group will be asked to download and complete the quest in the “SteWARdS Antibiotic Defence” app within 2 weeks on their smartphones. “SteWARdS Antibiotic Defence” is an evidence-based serious game app developed by the study team. The app will deliver bite-sized information on (1) the management of upper respiratory tract infections (URTIs), (2) appropriate antibiotic use, and (3) development of AMR to users as they complete the game quest (refer to the section on “Serious Game App Intervention”). Participants randomized to the control group will not be required to download the app. All participants will be followed up for 6-10 weeks to assess the effects of short-term knowledge retention. The design of the trial is presented in Figure 1.

**Figure 1 figure1:**
[figure not shown]
Trial schedule. KAP: knowledge of, attitude toward, and perception.

### Recruitment

#### Study Setting

We will recruit patients or their caregivers from government-funded primary care clinics (ie, polyclinics) in Singapore. These polyclinics manage 20% of Singapore’s primary health care needs by providing subsidized services such as medical treatment for acute and chronic conditions, vaccinations, and health education [19]. The conditions seen at the polyclinics are acute and are managed outside the health care setting (eg, at home) after consultation with a health care provider. Hence, the intervention will occur outside the health care setting.

#### Inclusion and Exclusion Criteria

Participants must be older than 18 years, be a visitor of National Healthcare Group (NHG) polyclinic, have access to an Android smartphone, and be able to comprehend the English language to be eligible for the study. Those who are unable to install Android app, not proficient with smartphone apps, and have visual or cognitive impairment will be excluded from the study.

#### Randomization and Blinding

Participants will be block randomized into the intervention or control group (4 participants per block) by drawing lots from a box. They will not be blinded from the randomization as the study team has to explain the study to them. Only participants assigned to the intervention group have access to the serious game app.

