### Study Procedures

We will randomize participants who are eligible for the study into the control or intervention group and collect their personal details in a password-protected file. Their demographic information will be collected on FormSG, a trusted web-based form manager developed by the Singapore government to collect survey data securely. We will require all participants to complete a 10-minute baseline KAP survey. For participants randomized into the intervention group, a study team member will assist participants in installing the “SteWARdS Antibiotic Defence” app on their mobile phones and provide further instructions regarding the game quest. Participants will need to complete the game quest in the app within 2 weeks, after which they will need to complete the postgame knowledge and an app satisfaction survey to complete the intervention. Participants will be contacted 6-10 weeks after completing the game quest and be asked to complete a 10-minute postintervention KAP survey.

Control group participants will complete a 10-minute baseline KAP survey and be contacted 6-10 weeks after recruitment to complete another 10-minute KAP survey. Participants will receive personalized messages via WhatsApp with a FormSG survey link and instructions to complete the postintervention survey during the study follow-up. We will provide reimbursement to all participants for their participation in the study. Reimbursement is structured according to behavioral economics principles to motivate participants to complete the intervention [24]. For example, reimbursement is divided over smaller amounts and is tiered to a higher value as the participant completes tasks toward the completion of the study. If the participant withdraws from the study, he or she will be asked to uninstall the app and will not be further contacted other than for reimbursement. The data collected prior to study withdrawal will be used for intention-to-treat analysis.

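### A constant block of 4 in an open trial lets a recruiter who sees every draw know up to a third of allocations in advance, and the baseline survey is listed after randomisation

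*Protocol article*

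**What the plan says.** All references are to the protocol article.

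- **Allocation method.** Randomization and Blinding: "Participants will be block randomized into the intervention or control group (4 participants per block) by drawing lots from a box". The Abstract (Methods) gives the same single block size, "Participants are randomized in blocks of 4 and into the intervention or control group", and describes a "parallel 2-armed randomized controlled trial with a 1:1 allocation".
- **Blinding.** Randomization and Blinding, on participants: "They will not be blinded from the randomization as the study team has to explain the study to them". Study Procedures adds that a team member helps intervention participants install the app, so staff also learn the arm at enrolment.
- **Eligibility.** Inclusion and Exclusion Criteria rules out people who cannot install an Android app and those "not proficient with smartphone apps". No threshold is given for proficiency.
- **Order of steps.** Study Procedures opens with "We will randomize participants who are eligible for the study into the control or intervention group and collect their personal details". It then covers the demographic form, then says "We will require all participants to complete a 10-minute baseline KAP survey", and then turns to installing the app in the intervention group.
- **Use of the baseline.** Primary Outcomes defines the primary outcome as the change in KAP from baseline to 6-10 weeks, measured by the KAP survey.

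**The concern.** There are two linked weaknesses, and the text supports them to different degrees.

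The first is predictability. If the block size is constant and known, and every allocation becomes visible as it is made, the remaining lots in a block follow from those already drawn. Hiding the lots in a box does not help once one arm's two lots are gone. A recruiter who knows the next arm could, knowingly or not, judge a visitor's proficiency with apps more or less strictly. The arms could then differ in familiarity with technology, and in whatever goes with it, before the intervention starts.

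The second is the timing of the baseline. If the KAP survey is answered after the participant knows the arm, that knowledge can affect effort or answers. The baseline is half of the primary change outcome. A shift at baseline in one arm passes into that arm's change score with the opposite sign, and adjusting for the affected baseline would not in general remove it.

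**Working it through.** The plan gives no figure for predictability, so there is none to reproduce. The inputs are the block size of 4 (Abstract; Randomization and Blinding), 1:1 allocation (Abstract) and 400 participants (Abstract; Sample Size, 200 per group). These give 400 / 4 = 100 blocks of 2 + 2.

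**Step 1: allocations known with certainty, block of 4.** There are 6 equally likely orders of two lots per arm. An allocation is certain when both lots of one arm have already gone.

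| Position in block | Chance that the arm is certain | Chance that the best guess is right |
|---|---|---|
| 1 | 0 | 1/2 |
| 2 | 0 | 2/3 |
| 3 | 1/3 (first two lots match) | 1/3 × 1 + 2/3 × 1/2 = 2/3 |
| 4 | 1 | 1 |

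- Certain per block: 0 + 0 + 1/3 + 1 = 1.333. As a share: 1.333 / 4 = 33.3%.
- Over the trial: 100 × 1.333 = about 133 of 400.
- Best-guess accuracy: (1/2 + 2/3 + 2/3 + 1) / 4 = 70.8%, against 50% for an unpredictable sequence.

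**Step 2: what longer constant blocks would give.** The same enumeration gives 25.0% for a block of 6 (1.5 per block, 100 of 400) and 20.0% for a block of 8 (1.6 per block, 80 of 400). Lengthening a constant block helps only modestly.

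**Step 3: what randomly varying blocks would give.** Take an observer who knows which sizes are in use and where the current block began, but not its size, with sizes equally likely. An allocation is then certain only in a block of the largest size, once one arm is exhausted there.

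- Sizes 4 and 6: 1.5 / (4 + 6) = 15.0%, or 60 of 400.
- Sizes 4, 6 and 8: 1.6 / (4 + 6 + 8) = 8.9%, or about 36 of 400.

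Simulation of both schemes gave 15.0% and 8.9%.

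**Step 4: baseline timing.** No arithmetic applies. In Study Procedures the sequence is randomisation with collection of personal details, the demographic form, the baseline survey for everyone, then app installation. A later sentence again describes the baseline survey as something control-group participants complete, which fits that order. No sentence shown places the survey before the draw. On the other hand, no word such as then or after joins randomisation to the survey, and the trial schedule (Figure 1) is not shown.

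**The case against.** The strongest case on the other side has five parts.

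- **One third assumes an ideally informed recruiter.** The article recruits from more than one polyclinic and does not say who draws, how many boxes there are or whether draws are made singly. This stands. A reader might infer that staff will in fact know 133 allocations. The documents support only that they could know up to that many, and nothing shows that enrolment would be steered.
- **Eligibility comes before the draw.** Study Procedures randomises those already eligible, and inability to install the app is an eligibility exclusion. This stands too. A reader might infer that the people who judge proficiency also run the draw, or that unsuitable app users are removed after allocation. The article says neither. What remains is anticipation of the next lot while a visitor is being screened.
- **The order of the baseline is inferred.** It rests on the sequence of sentences. That is the natural reading but not proof. The 11 in-app knowledge items do follow allocation, and a reader might take them as settling the matter. They do not, because the primary outcome is defined by the KAP survey that all participants complete.
- **No bias has been shown.** A reader might infer that the result would favour the app. The direction is open: if app-arm participants tried harder at baseline, their change score would be reduced.
- **An article leaves concealment detail to the full protocol.** That is fair for who holds the lots and in what container. It does not cover the constant block of 4, which the article states twice.

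**Conclusion.** The point stands in a limited form. The constant block of 4 in an open trial is a stated design choice, and it makes up to one third of allocations, up to about 133 of 400, knowable in advance. The ceiling assumes lots drawn without replacement within each 2 + 2 block, one participant at a time, by a recruiter who has seen every earlier draw from the same box and knows where each block starts. The number is smaller where recruiters do not see each other's draws or a block is drawn at once. It measures opportunity for selection, not bias in the KAP result.

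That the baseline survey follows allocation is how Study Procedures reads, but this needs confirmation. The direction and size of any effect on the primary outcome cannot be derived from the document. The point is worth correcting because the remedy is cheap, but it does not by itself invalidate the comparison.

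**What to change.** 1. Replace the constant block of 4 with randomly varying block sizes, for example 4, 6 and 8, taken from a list concealed from recruiters, and do not disclose the sizes during recruitment. On the assumptions in the working, the share of certain allocations falls from 33.3% to about 9%.
2. State in Study Procedures that allocation is revealed only after eligibility, consent and the submitted baseline KAP survey have been recorded for that participant. If this is already the practice, correcting the wording is enough.

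The cost is minor preparation of the list and of the concealment. The final group sizes may also differ slightly: an unfinished block of 8 leaves a difference of at most 4 participants per list, against 2 for an unfinished block of 4. With about 200 per group this has a negligible effect on power.
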